#### **12.1.3. Vital Signs and Body Measurements**

##### **Vital Signs**

Vital signs will be assessed according to the Schedule of Evaluations (see [Table 2](#)).

Measurements will include the following:

- Body temperature (°C)
- Respiratory rate
- Seated blood pressure (systolic and diastolic) –after being seated for approximately 5 minutes
- Seated pulse - after being seated for approximately 5 minutes

If the first vital sign value(s) is abnormal during Visit 1 (screening); the vital sign measurement(s) will need to be repeated. If the vital sign measurement(s) continue(s) to be abnormal (as defined in Section 7.2, Patient Exclusion Criteria), the patient will be excluded from the study.

After the patient signs the informed consent, vital sign values that the Investigator considers clinically significant will be recorded as adverse events for the patients that are enrolled into the study. Vital sign values considered to be potentially clinically notable are provided in [Appendix 21.2](#) for the Investigator's guidance. The recording must be in the form of a clinical sign, symptom, or diagnosis, and not a mere description of the vital sign abnormality. Measurements will be repeated at medically appropriate intervals until they return to acceptable levels.

##### **Body Measurements**

Body measurements will be performed according to the Schedule of Evaluations (see [Table 2](#)).

- Body weight (kg) (at screening, Night 1, and EOS or ET)
- Height (cm) (at screening only)

#### **12.1.4. Medical History and Physical Examinations**

A full physical examination will be performed at screening and EOS or ET. An abbreviated physical examination will be conducted on Night 1 only if the patient reports a change in health or experiences an AE. Documentation of the physical examination will be included in the source documentation at the investigational site. Findings at screening will be recorded as medical history on the electronic CRF. Only changes from baseline physical examination findings that meet the definition of an adverse event will be recorded on the Adverse Events electronic CRF.

#### **12.1.5. Electrocardiograms (ECGs)**

A standard, resting 12-lead ECG will be obtained for each patient at the visits designated on the Schedule of Evaluations (see [Table 2](#)). A central facility will be used in this study for interpretation and analysis of ECGs. The time the ECG is performed will be recorded (using a 24-hr clock). Two original ECG tracings will be produced; one will be retained in the patient's clinical record, and the other will be kept for submission to the central ECG facility for reading as needed (in the event automated submission to central ECG facility can not be transmitted). Details concerning the ECG recording instructions will be provided to all Investigators in a separate manual prior to the start of the study.

To ensure accuracy in the ECG reading at baseline (Night 1), the ECG should be performed 3 times (about 5 minutes apart), whereas a single ECG reading is sufficient for other visits unless a clinically significant finding is present.

#### **12.1.6. Pregnancy**

Before enrolling a female of child-bearing potential in this clinical study, Investigators must review the following information with the patient:

- Informed consent requirements
- Risk of pregnancy
- Current contraceptive use
- Drug interactions with hormonal contraceptives
- Pregnancy prevention during the study

All females of child bearing potential, (defined as any female unless surgically sterile or postmenopausal at least 12 months) must be instructed to contact the Investigator immediately if they suspect they might be pregnant while participating in this study. Any pregnancy that occurs during study participation must be reported to Covance Drug Safety Services (Vanda's designee) using a Pregnancy Report and Paternal Exposure Form within 24 hours of learning of its occurrence and must be followed to determine outcome. If a patient becomes pregnant, she will be discontinued from the study.

Women using hormonal methods of birth control (e.g. oral contraceptives, patch and steroids) must use an additional method of birth control during the study and for one month after the last dose. *In vitro* data suggests that VEC-162 could potentially induce the enzyme CYP3A4/5 which metabolizes hormonal contraceptives.

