| Investigational product, dosage and mode of administration:
VEC-162 will be administered orally as doses of 20 mg or 50 mg. All capsules will be size 1 and the color will be opaque.                                                                                                                                                                                                   |                                     |
| Duration of treatment:
Up to 47 days total: 7-days ( $\pm$ 2 days) of single-blind placebo lead-in, 35-days ( $\pm$ 2 days) of double-blind study treatment and 1-day of single-blind placebo wash-out period.                                                                                                                                                                          |                                     |
| Reference therapy, dosage and mode of administration:
Placebo capsules will be provided in size and appearance identical to those containing VEC-162 and will be administered orally.                                                                                                                                                                                                   |                                     |
| Objectives:
Primary:
1. To assess the effects of 20 and 50 mg VEC-162 on the average latency to persistent sleep (LPS) as measured by polysomnography (PSG) on Nights 1 and 8.
Secondary:
1. To assess the effects of 20 and 50 mg VEC-162 on the average Wake After Sleep Onset (WASO), total sleep time (TST), and sleep efficiency (SE) as measured by PSG on |                                     |

Nights 1 and 8.

2. To assess the maintenance of effect of oral doses of 20 and 50 mg VEC-162 on the average LPS, WASO, TST, and SE as measured by PSG on Nights 22 and 29.
3. To assess the effects of 20 and 50 mg VEC-162 on PSG parameters for each individual evaluation night.
4. To assess the effects of single and multiple oral doses of 20 and 50 mg VEC-162 on subjective assessments such as sleep quality, depth of sleep, sleep latency, total sleep time, daytime function and daytime alertness.
5. To assess the next day residual effects of oral doses of 20 and 50 mg VEC-162 as measured by digit symbol substitution test (DSST) and visual analog scale (VAS).
6. To examine the potential rebound effects upon abrupt treatment cessation after 5 weeks of VEC-162 as measured by PSG.

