## **7. SELECTION AND WITHDRAWAL OF PATIENTS**

### **7.1. Patient Inclusion Criteria**

Each patient must meet the following criteria for inclusion in the study:

1. Ability and acceptance to provide written informed consent;
2. Men or women between 18 – 64 years, inclusive;
3. Body Mass Index (BMI) of  $>18$  and  $<33\text{kg/m}^2$  ( $\text{BMI} = \text{weight (kg)} / [\text{height (m)}]^2$ );
4. Women of child-bearing potential (defined as less than 1 year post-menopausal or not surgically sterile) must be using an acceptable method of birth control (e.g., oral contraceptives, steroids, patch, intrauterine device [IUD], diaphragm or condom with spermicidal jelly or foam or abstinence, surgical sterility, or cervical cap) for a period of 35 days before the first dosing and must have a negative pregnancy test at the screening and Night 1 visits;

*Note:* Women using hormonal methods of birth control (e.g. oral contraceptives, patch, and steroids) must use an additional method of birth control during the study and for one month after the last dose.

5. Meets diagnostic criteria for primary insomnia as defined in DSM-IV;
6. Subjective sleep latency of  $\geq 45$  minutes at least 3 nights/week **and** subjective total sleep time  $\leq 6.5$  hours of sleep at least 3 nights/week based on sleep history (30 days prior to the screening visit);
7. Subjective sleep latency of  $\geq 45$  minutes at least 3 nights/week **and** subjective total sleep time  $\leq 6.5$  hours of sleep at least 3 nights/week based on sleep diary;
  - a. Note: The data from the seven consecutive days immediately preceding Visit 2 must be used for this criterion. The patient must have completed the sleep diary for at least 4 days out of the seven.
8. A mean LPS of  $\geq 30$  minutes on two consecutive placebo lead-in PSG with no night having a LPS less than 20 minutes;
9. Habitual bedtime between 9:00 PM and 1:00 AM at screening for at least one month prior to screening;
10. No history or evidence of restless leg syndrome or periodic limb movement disorder based on a Periodic Limb Movement with Arousal Index (PLMAI) score  $>10$  on diagnostic PSG;
11. No history or evidence of sleep apnea based on Apnea-Hypopnea Index (AHI) score  $>10$  on diagnostic PSG;
12. Willing and able to comply with study requirements and restrictions.

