#### **During the Wash-out Period:**

- A single oral dose of placebo will be administered to the patients on Visit 7 (Night 36  $\pm$  2 days) 30 minutes ( $\pm$  5 minutes) prior to lights off under single-blind conditions. The placebo capsule will be taken with water.

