### 12.4.2. Post-study Adverse Event

At the last scheduled visit, the Investigator should instruct each patient to report any subsequent event(s) that the patient or the patient’s personal physician believes might reasonably be related to participation in this study. The Investigator should notify the study sponsor of any death or adverse event occurring at any time after a patient has discontinued or terminated study participation that may reasonably be related to this study. The Investigator should also notify the sponsor if they become aware of the development of cancer or a congenital anomaly in any offspring conceived subsequent to a patient’s study participation.

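### Section 12.1.6 stops pregnancy call-in and reporting at the end of study participation, although the protocol's own contraceptive-interaction precaution runs one month past the last dose

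*Protocol*

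**What the plan says.** Section 12.1.6 holds the three statements that matter.

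- **Instruction to the patient.** Women of child-bearing potential "must be instructed to contact the Investigator immediately if they suspect they might be pregnant while participating in this study".
- **Duty of the site.** "Any pregnancy that occurs during study participation must be reported to Covance Drug Safety Services", on a named form, "within 24 hours of learning of its occurrence and must be followed to determine outcome".
- **Precaution.** Women on hormonal contraception "must use an additional method of birth control during the study and for one month after the last dose". The Note to inclusion criterion 4 (section 7.1) sets the same requirement. The reason given in 12.1.6 is that in vitro data suggest VEC-162 "could potentially induce the enzyme CYP3A4/5 which metabolizes hormonal contraceptives".

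The last scheduled visit is Visit 7. A placebo capsule is given on Night 36 (section 8.1), and end-of-study procedures, including the last serum pregnancy test, follow on the morning of Day 37 (section 10.2.2 and Table 2). A patient who stops early has the serum test at the early-termination visit (section 10.2.3). No later test or contact is scheduled in either case.

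Two general provisions reach beyond the last visit. Section 12.2.4 has the site record new adverse events for 7 days and new serious adverse events for 30 days. Section 12.4.2 has patients told at the last visit to report later events thought to be related to the study. It also asks investigators to notify the sponsor of related events at any time, and of a congenital anomaly in "any offspring conceived subsequent to" participation.

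**The concern.** The protocol names a mechanism by which hormonal contraception might fail and says how long the added precaution must last. An unintended pregnancy in that period is the event by which such a failure would show itself. The pregnancy rules in the same section end with participation, so for most of that month a site that follows 12.1.6 exactly has no duty to collect the event, and the woman has no pregnancy-specific instruction to report it.

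What is at stake is the completeness of safety data on pregnancies in the period the protocol itself treats as needing extra protection. No endpoint, hypothesis test or sample-size figure is affected.

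**Working it through.** **Inputs**

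- Treatment duration: "Up to 47 days total", made up of 7 (±2) days of lead-in, 35 (±2) days of double-blind treatment and 1 day of wash-out (Synopsis).
- Last active dose: nominally Night 35. Last capsule of any kind: "A single oral dose of placebo will be administered to the patients on Visit 7", nominally Night 36 (section 8.1).
- Last visit and last pregnancy test: nominally Day 37, with a 2-day visit window (section 10.2.2, Table 2).
- Post-visit recording: 7 days for adverse events, 30 days for serious adverse events (section 12.2.4).
- Assumption: one month is 28 to 31 days, with 30 as the central value. The protocol does not define it.
- Assumption: participation ends on Day 37. This is inferred from the last scheduled visit.

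**Check of the plan's own figure.** (7 + 2) + (35 + 2) + 1 = 47 days, which matches the Synopsis.

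**Share of the month after Day 37.** Uncovered days = last dose + month − 37; share = uncovered days / month.

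| Month (days) | Counted from | Month ends | Days after Day 37 | Share |
|---|---|---|---|---|
| 28 | last active dose, Night 35 | Day 63 | 26 | 92.9% |
| 30 | last active dose, Night 35 | Day 65 | 28 | 93.3% |
| 31 | last active dose, Night 35 | Day 66 | 29 | 93.5% |
| 28 | last capsule, Night 36 | Day 64 | 27 | 96.4% |
| 30 | last capsule, Night 36 | Day 66 | 29 | 96.7% |
| 31 | last capsule, Night 36 | Day 67 | 30 | 96.8% |

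**Do the general provisions fill the gap?**

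- *Adverse events, 7 days (to 37 + 7 = Day 44).* Suppose pregnancy is read as an adverse event; section 7.3 does list it under adverse events as a reason for discontinuation. Then 19 of 28 days (67.9%) remain uncovered at the low end, 21 of 30 (70.0%) and 22 of 30 (73.3%) for a 30-day month from the two starting points, and 23 of 31 (74.2%) at the high end.
- *Serious adverse events, 30 days (to 37 + 30 = Day 67).* This spans the whole month in every row. But an uncomplicated pregnancy meets none of the criteria in Table 4, so it is not reportable by this route.
- *Section 12.4.2.* It has no time limit, but it depends on the patient or her physician believing the event to be related. It does not mention pregnancy as such.

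**Pregnancies conceived during participation.** The duty attaches to when the pregnancy occurs, and the 24 hours run from when the site learns of it, with no end date for learning. A conception late in treatment that comes to light after Day 37 is therefore reportable and followed to outcome. What is absent is a prompt: the call-in instruction has lapsed and no later test exists. How many conceptions would be too recent for the Day 37 test depends on a detection lag that the protocol does not give. If it were 8 to 14 days, conceptions on Days 30–35 (6 of 35 treatment days, 17%) to Days 24–35 (12 of 35, 34%) would still test negative. This is illustrative only, and the conclusion does not rest on it.

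**The case against.** The strongest reply is that a contraception period and a pregnancy-reporting period serve different purposes, so a difference in length is not in itself a contradiction, and that the protocol is not silent after Day 37. Section 12.4.2 gives every patient an open-ended instruction to report events thought related. Section 12.1.6 has the investigator discuss interactions with hormonal contraceptives before enrolment, so a woman whose contraception failed might well make the connection. Serious outcomes within 30 days fall under 12.2.4, and a congenital anomaly is a serious adverse event under Table 4. The month also binds only users of hormonal contraception, who are required to use a second method throughout it, and 93–97% is a share of calendar days, not of pregnancies lost.

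Most of this stands, and it rules out several stronger conclusions that a reader might draw:

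- *That the last on-treatment conceptions fall outside the reporting rule.* They do not; they occur during participation and remain reportable whenever learned of.
- *That 12.4.2 covers only congenital anomalies.* It also covers any later event believed related.
- *That offspring conceived during the study are left out.* Once their pregnancies are known, 12.1.6 has them followed to outcome.
- *That drug-exposed pregnancies after the last dose would be missed.* The protocol gives no half-life from which exposure weeks later could be judged.
- *That pregnancies in partners of male patients are lost.* The call-in instruction is addressed to women only, but the reporting sentence is not so limited and the form's title includes paternal exposure. The study manual and consent text are not available to settle it.

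What the reply does not remove is that no provision expressly requires an uncomplicated pregnancy arising in the precaution month to be called in, reported or followed. Capture there is passive and depends on someone judging it related.

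**Conclusion.** The point holds as a mismatch of windows within 12.1.6. The precaution runs to about Day 63–67, while the pregnancy-specific instruction and duty end with participation, nominally Day 37. That leaves 28 to 29 of 30 days (93–97% across month lengths and starting points) without a pregnancy-specific rule, or 68–74% if pregnancy is treated as an adverse event with 7 days of recording.

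This rests on taking Day 37 as the end of participation and on the nominal visit schedule, and it concerns women using hormonal contraception. The number of pregnancies involved cannot be estimated from the protocol. The effect is on completeness of safety follow-up, and the change is an inexpensive improvement worth making.

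**What to change.** In 12.1.6, reconcile the reporting window with the protocol's own one-month window. Women are told to call about any suspected pregnancy, and sites must report within 24 hours of learning and follow to outcome, for any pregnancy occurring from first dose to one month after the last dose. State whether the last dose means the last active dose or the Night 36 placebo capsule. The contraception requirement itself stays as it is.

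Two optional clarifications could go in at the same time: say in 12.1.6 whether pregnancies in partners of male patients are to be reported, and word the offspring clause in 12.4.2 so that it covers conception during as well as after participation.

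The cost is protocol and consent wording. The form and the safety reporting route already exist. The downside is a few extra pregnancy follow-ups after Day 37.

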## 12.2. Definitions Related to Safety

### 12.2.1. Adverse Event

An **adverse event** (AE) is defined as any untoward medical occurrence in a clinical investigation patient that does not necessarily have casual relationship with treatment. An AE can therefore be any unfavorable and unintended sign (including clinically significant abnormal laboratory finding), symptom, or disease temporally associated with clinical study whether or not related to the investigational product.

Every attempt should be made to describe the AE in the form of a diagnosis. If a clear diagnosis has been made, individual signs and symptoms will not be recorded unless they represent atypical or extreme manifestations of the diagnosis, in which case they should be reported as separate events. If a clear diagnosis cannot be established, each sign and symptom must be reported individually.

### 12.2.2. Serious Adverse Event

Adverse events are classified as serious or non-serious. A **serious adverse event** is defined as any untoward medical occurrence that occurs during clinical study that meets one of the following criteria:

**Table 4: SAE Criteria and Definitions**

| SAE Criteria                                                          | Definition                                                                                                                                                                                                                                                                                                                                                                  |
|-----------------------------------------------------------------------|-----------------------------------------------------------------------------------------------------------------------------------------------------------------------------------------------------------------------------------------------------------------------------------------------------------------------------------------------------------------------------|
| Death of Patient                                                      | An event that results in the death of the patient.                                                                                                                                                                                                                                                                                                                          |
| Life-Threatening                                                      | An event that, in the opinion of the Investigator, would have resulted in immediate fatality if medical intervention had not been taken. This does not include an event that would have been fatal if it had occurred in a more severe form.                                                                                                                                |
| Hospitalization                                                       | An event that results in an admission to the hospital for any length of time. This does not include an emergency room visit or admission to an outpatient facility.                                                                                                                                                                                                         |
| Prolongation of Hospitalization                                       | An event that occurs while the patient is hospitalized and prolongs the patient's hospital stay.                                                                                                                                                                                                                                                                            |
| Congenital Anomaly/Birth Defect                                       | An anomaly detected at or after birth, or any anomaly that results in fetal loss.                                                                                                                                                                                                                                                                                           |
| Persistent or Significant Disability/Incapacity                       | An event that results in a condition that substantially interferes with the activities of daily living of a study patient. Disability is not intended to include transient interruptions of daily activities or experiences of relatively minor medical significance such as headache, nausea, vomiting, diarrhea, influenza, and accidental trauma (e.g., sprained ankle). |
| Important Medical Event Requiring Medical or Surgical Intervention to | An important medical event that, based on medical judgment, may not be immediately life-threatening or result in death or hospitalization, but may jeopardize the patient and may require medical or surgical intervention to                                                                                                                                               |

| SAE Criteria            | Definition                                                                                                                                                                                                                          |
|-------------------------|-------------------------------------------------------------------------------------------------------------------------------------------------------------------------------------------------------------------------------------|
| Prevent Serious Outcome | prevent any of the outcomes listed above (i.e., death of a patient, life-threatening, inpatient hospitalization, prolongation of existing hospitalization, congenital anomaly, or persistent or significant disability/incapacity). |

All AEs that do not meet the above criteria should be classified as ***non-serious adverse events***.

